After screening, suitable participants will be randomly assigned to the 3.0 g/day UGSJB or placebo group. UGSJB granule is composed of nine herbs: Ban Xia (*Pinellia ternate*), Bai Zhu (*Atractylodes japonica*), Fu Ling (*Poria cocos*), Dang Gui (*Angelica gigas*), Chen Pi (*Citrus unshiu*), Chuan Xiong (*Cnidium officinale*), Diao Gou Teng (*Uncaria sinensis*), Chai Hu (*Bupleurum falcatum*), and Gan Cao (*Glycyrrhiza glabra*) (Table 1). Placebo granule is composed of 0.95 g lactose, 0.4 g corn starch, and 0.15 g caramel pigment to match the UGSJB. UGSJB and placebo granules were manufactured and stored by Kyungjin Pharmaceutical Co., Ltd. (Gyeonggi, Republic of Korea). The solvent used in the extract was purified water, and the ratio of extract to herbal drugs was about 12.2%. Storage, dispensation, and quality control of the UGSJB and placebo granules were carried out by a blinded pharmacist in each study center. Caregivers will be instructed to dissolve in water and administer one pack (1.5 g) of UGSJB or placebo granule after breakfast and dinner for 12 weeks, which was the period that reported effectiveness in previous studies [11, 12]. The dosage regimen was determined by referring to the authorization by the Ministry of Food and Drug Safety and the clinical judgment of Korean medicine doctors. The quantities of marker constituents per pack were 3.99 mg of glycyrrhizinate and 11.18 mg of hesperidin. Lead and microorganisms were not detected, and the concentration of arsenic was 0.33 parts per million in one pack of UGSJB. The UGSJB or placebo will be prescribed by Korean medicine doctors with more than 5 years of clinical experience. If there are any adverse events (AEs) related to UGSJB, such as pseudoaldosteronism, myopathy, allergic skin reaction, and gastrointestinal upset, that participant will stop taking medication and will receive appropriate treatment according to the severity of the AEs. The guardians should return the used as well as unopened packages to check the adherence to treatment.

**Table 1 Tab1:** Composition of Ukgansangajinpibanha granule

Plant name	Used part	Registration	Amount, grams
*Pinellia ternate* Breitenbach (Araceae)	Dried rhizome	KP	0.84
*Atractylodes japonica* Koidz. (Compositae)	Dried rhizome	KP	0.67
*Poria cocos* Wolf (Polyporaceae)	Dried scleorotia	KP	0.67
*Angelica gigas* Nakai (Umbelliferae)	Dried root	KP	0.5
*Citrus unshiu* Markovich (Rutaceae; citrus peel)	Dried fruit peel	KP	0.5

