### Safety assessment

To evaluate the safety of UGSJB, electrocardiogram and laboratory examinations (blood routine test, urine routine test, liver and kidney function test, and electrolytes) will be conducted on all participants at the screening phase (week 0) and post-treatment phase (week 12). At each visit, voluntarily reporting subjective or objective adverse symptoms will be collected to assess overall clinical safety by asking the question “Has there been any abnormal reactions since the last visit?” If participants drop out of our trial for treating any AEs, the AEs will be considered severe.

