### Sample size calculation

In Zhou *et al*. (2015) [32], an RCT on autistic children (average age of 4.75 years) was conducted to measure the CARS before and after the interventions in the herbal medicine–plus–behavioral education group and the behavioral education–alone group. The changes in CARS were −7.9 ± 5.42 for combination therapy and −4.6 ± 5.53 for behavioral education alone. For the purpose of calculating the standard deviation of the CARS change, the before-after correlation coefficient was assumed to be 0.33, referring to Sun *et al*. (2016) [33]. The sample size was calculated by using a two-tailed 5% significance level, 80% power, and 1:1 allocation by PASS 14 (NCSS Statistical Software, Kaysville, UT, USA). The alternative hypothesis was established that the change in CARS for 12 weeks between the experimental group and the control group was not the same. The required number of subjects per group is 45, and the total number of enrolled subjects is 120 (60 in each group), allowing for a 25% withdrawal rate.

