### Statistical analysis

Data coding will be kept by the researcher team, and data analysis will be conducted by statisticians who are independent of the research team. Effectiveness data will be analyzed mainly with full analysis set (FAS) and further analyzed with per protocol set (PPS). The FAS is defined as all subjects who have taken at least one prescription in the clinical trial and have at least one measurement of the primary outcome after having the prescription. The PPS is defined as all subjects who have taken more than 118 packs (70% of the total 168 packs). The safety analysis includes all data from the participants who have taken at least one prescription in the clinical trial.

Continuous data will be presented as descriptive statistics such as mean and standard deviation, and any statistical differences between the two groups will be tested by using the independent *t* test or Wilcoxon rank-sum test. Categorical data will be presented as frequency and percentage, and any statistical differences between the two groups will be tested by using the chi-squared test or Fisher’s exact test. If significant differences of baseline are recognized between two groups, analysis of covariance (ANCOVA) or rank ANCOVA will be used. In secondary analyses within groups, continuous data will be analyzed by using the paired *t* test or Wilcoxon signed-rank test, and categorical data will be analyzed by using McNemar’s test.

The significance level is 0.05 for all statistical tests, and two-tailed tests will be performed. Missing values will be imputed by the last-observation-carried-forward method.

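### An AE is classed as severe when the child leaves the trial to have it treated, whatever its intensity, so the severe-AE count would mix intensity with disposition.

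*Protocol article*

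**What the plan says.** The Safety assessment section of the protocol article describes how AEs are collected: at each visit one open question is asked, and "voluntarily reporting subjective or objective adverse symptoms will be collected to assess overall clinical safety". It then fixes a severity label by what happens to the participant: "If participants drop out of our trial for treating any AEs, the AEs will be considered severe". The article neither limits this sentence to certain events nor ties it to an intensity grade.

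The Interventions section covers AEs related to UGSJB, with examples "such as pseudoaldosteronism, myopathy, allergic skin reaction, and gastrointestinal upset". For these it says "that participant will stop taking medication and will receive appropriate treatment according to the severity of the AEs".

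The Statistical analysis section defines the safety population: "The safety analysis includes all data from the participants who have taken at least one prescription in the clinical trial". AEs in children who later leave therefore stay in the safety results, with whatever severity label they were given.

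**The concern.** Severity normally describes how intense an event is. Whether the event ended treatment or participation is a separate fact, and both are worth knowing. The sentence in Safety assessment merges them: leaving the trial for treatment of an AE is enough to make that AE severe.

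Safety is named in the article's title and is a stated aim. A reader who sees a count of severe AEs will take it as a count of intense events. Under this rule it would also contain mild or moderate events in children who left to be treated. The rule covers all AEs, not only those attributed to the granule. Both arms have 24 acupuncture sessions, so an acupuncture-related or unrelated event could be relabelled in the same way.

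**Working it through.** No power, alpha or event figure is involved, so the check is a comparison of the statements, followed by a note on scale.

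**1. Two uses of severity.** In Interventions, severity comes first and directs treatment, which presumes that it is a property of the event. In Safety assessment, disposition comes first and sets severity. The two can coexist only if one word carries two meanings.

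**2. What the rule does to each kind of event.**

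| Clinical intensity | Child stays in trial | Child leaves for treatment of the AE |
|---|---|---|
| Mild or moderate | Label not changed by the rule | Severe under the rule |
| Severe | Label not changed by the rule | Severe under the rule and by intensity |

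The rule and intensity grading disagree in one cell: a mild or moderate event in a child who leaves for treatment. The disagreement only moves events upward.

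**3. What the count then measures.** In one arm, let S be the number of AEs that are severe by intensity, and M the number of mild or moderate AEs for which the child left to be treated. The count under the rule is S + M. Writing U for UGSJB and P for placebo, the arm difference is (S_U − S_P) + (M_U − M_P). Both terms compare randomised groups, so the difference is a valid comparison, but of a composite. Without a separate record of M, the two parts cannot be told apart.

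**4. Do relabelled events reach the results?** Yes. The safety population includes everyone with at least one prescription, so nothing removes them.

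**5. Can M be sized?** The only related figure is in Sample size calculation, which gives 45 evaluable and 60 enrolled children per group, "allowing for a 25% withdrawal rate". This reproduces: 45 / (1 − 0.25) = 60, leaving 60 − 45 = 15 withdrawals per group, or 30 of 120 in total. These are withdrawals for all reasons. The article does not say how many would be for treatment of an AE, nor how many of those AEs would be mild or moderate. If withdrawals ran as planned, the children affected per group could be anywhere from 0 to 15 (0% to 25%). That range is too wide to serve as an estimate. It is not a strict bound either, since actual withdrawal may differ from the allowance.

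**The case against.** The strongest reply is that the rule is narrow and harmless. It applies only when a child leaves *for treating* an AE, it is applied alike in both arms by blinded staff, and it can only overstate harm. No severe-AE rate is named as an outcome, and no event is lost. The article is also condensed: a grading scale may stand in the full protocol, with this sentence as one added criterion on top of it.

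Much of this stands, and it rules out several stronger readings that a reader might infer:

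- *Every AE that leads to drop-out becomes severe.* The trigger is leaving to have the AE treated. A child whose guardian is simply put off by an untreated mild upset is not clearly covered.
- *Stopping medication triggers the label.* Interventions stops the medication after a related AE. It does not say that the child leaves the trial, so the mandated stop alone does not make an event severe. A child taken off the granule might be more likely to leave, but that is inference.
- *The arms are no longer comparable.* The Blinding section covers subjects, acupuncturists, data collectors and analysts, and the same rule holds in both arms. The randomised comparison stays valid.
- *Up to a quarter of an arm would be mislabelled.* The 25% is an all-cause planning allowance. Reaching it would require every withdrawal to be for treatment of a non-severe AE.
- *The article fails to give a grading scale.* Such a scale is commonly left to the full protocol, and its absence here is no finding.

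What does not stand is that the sentence is therefore harmless. If a full scale exists, this sentence overrides or contradicts it for some events. Erring toward more harm is not neutral either: events that are severe by intensity become harder to pick out when milder ones carry the same label.

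**Conclusion.** The point holds in this limited form. The article states a rule that sets severity by disposition, while another section treats severity as a property of the event. If drop-outs for AE treatment occur, mild or moderate events would be counted as severe, and equally intense events in children who stay would not. The severe-AE count would then be hard to interpret and hard to compare with trials that grade on intensity.

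The number affected cannot be estimated from the document and may be zero. The conclusion assumes that the sentence is applied as written, and that severity will be reported in some form. It does not depend on any reading of the stopping rule. The randomised, blinded comparison between arms and the primary efficacy analysis are not affected. The point is worth correcting because it touches a title objective and costs little.

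**What to change.** Replace the sentence in Safety assessment with two separate provisions:

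- Severity of every AE is graded on clinical intensity, by blinded assessors, without regard to whether the child stops medication or leaves the trial.
- AEs leading to discontinuation of study medication or to withdrawal from the trial are recorded as such and tabulated by arm as a category of their own.

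Reconcile the wording so that severity means the same thing in Safety assessment and Interventions. If the full protocol already defines a scale, refer to it. No change to the stopping rule is proposed.

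The second provision keeps what the present sentence seems meant to capture, namely which AEs ended participation, so no information is lost. The cost is a small change to protocol and case report form wording; no visit or clinical test is added.

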### Economic evaluation

Cost-effectiveness analysis (CEA), cost-utility analysis (CUA), and cost-benefit analysis (CBA) will be carried out for the economic evaluation. Cost variables include medical and non-medical costs of patients and cost burden and productivity losses of guardians. Effectiveness variables will be measured by ABC^2^, CARS, and CHQ-PF28. Utility variable will be measured by EQ-5D-Y proxy 1. The result of CEA will be calculated as the average cost-effectiveness ratio (ACER) or incremental cost-effectiveness ratio (ICER), and the result of CUA will be calculated as the average cost-utility ratio (ACUR). Intervention with the smallest ACER or ACUR will be selected. Intervention with ICER below a certain level will be considered cost-effective.

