Ukgansangajinpibanha (UGSJB), which is made from Ukgansan by adding Citri Pericarpium and Pinelliae Rhizoma, has been more often used in children with indigestion compared with Ukgansan. Similar to Ukgansan, it has been administered to angry, sensitive, nervous, and unsettled children with ASD [13]. Unlike Ukgansan, UGSJB is legitimately prescribed as an herbal formula granule for nervousness, insomnia, night crying, and malnutrition in South Korea and Japan [14]. Interestingly, children with ASD tend to experience more gastrointestinal symptoms than children without ASD [15]. Therefore, we prepared a well-designed clinical trial to investigate the safety and effectiveness of UGSJB on ASD symptoms compared with placebo treatment. The results of this trial will provide evidence of whether UGSJB is safe and effective for the treatment of ASD in children.

Acupuncture, a treatment supported by the National Health Service in South Korea, will be provided to every participant for an economic evaluation. Acupuncture has weak evidence of benefits but is a safe and effective treatment for ASD [16]. Frequently used acupoint for treating ASD sympstoms are EX-HN1, GV17, PC6, LR3, KI3, HT7, LU9, GV20, GV24, GV24.5, GB13, GB19, KI4, LR4, ST36, SP3, and SP6 [17]. We decided to use EX-HN1, GV20, and GV24 for acupuncture treatment of ASD in children because these acupoints have been frequently used in RCTs on ASD [18], and scalp acupuncture decreased scores of Childhood Autism Rating Scale (CARS) and Autism Behavior Checklist (ABC^1^) of children with ASD [19]. UGSJB in combination with acupuncture will be evaluated from an economic perspective.

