#### Child Health Questionnaire-Parent Report Form 28 (CHQ-PF28)

CHQ-PF28 has been used around the world as a tool to measure the general quality of life for children who are 5 or older. It has a verified internal consistency of 0.72 and a test-retest reliability of 0.31–0.84 [29]. The item scores are aggregated according to the calculation method set by HealthActCHQ, Inc. (Boston, MA, USA), and the higher score is interpreted as the higher quality of life. The assessment will be carried out during the visit of baseline (visit 2), mid-point (visit 14), termination (visit 25), and follow-up (visit 26).

#### EuroQoL Five-dimension Five-level Youth (EQ-5D-Y) proxy 1

EQ-5D-Y was transformed from EQ-5D to assess the quality of life of children and teens, and the proxy version is recommended for ages 4 to 7. The results of the multinational studies show that EQ-5D-Y has a test-retest reliability of 69.8–99.7%, Kappa coefficient of 0.67, and correlation coefficient of −0.56 with other tools [30]. Lower scores indicate better quality of life. The assessment will be carried out during the visit at baseline (visit 2), mid-point (visit 14), termination (visit 25), and follow-up (visit 26).

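### Selecting the arm with the smallest average cost ratio can name the wrong arm for an add-on treatment and can contradict the ICER criterion stated beside it; the CUA has no incremental ratio

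*Protocol article*

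**What the plan says.** All the rules at issue stand in the protocol article under Economic evaluation. Cost-effectiveness (CEA), cost-utility and cost-benefit (CBA) analyses are planned. For the inputs, "Effectiveness variables will be measured by ABC^2^, CARS, and CHQ-PF28" and "Utility variable will be measured by EQ-5D-Y proxy 1".

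The CEA may be reported as an average ratio (ACER) or an incremental one (ICER). For the CUA only an average ratio is named: "the result of CUA will be calculated as the average cost-utility ratio (ACUR").

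Two decision rules follow in consecutive sentences:

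- "Intervention with the smallest ACER or ACUR will be selected"
- "Intervention with ICER below a certain level will be considered cost-effective"

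The section does not say which rule prevails if they differ.

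On the comparison itself, Background, Interventions and Discussion all state that every participant receives acupuncture. Study participants gives one schedule of 24 treatment visits for all, and Interventions keeps existing treatments running. The economic aim in Background is worded accordingly: "UGSJB in combination with acupuncture will be evaluated from an economic perspective".

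**The concern.** The randomised contrast is UGSJB against placebo on top of care that both arms share. What a payer needs to know is what the extra effect costs. An average ratio instead divides each arm's whole cost, including the shared visits, guardian time and usual care, by that arm's whole effect. Ranking arms on it lets the shared cost and the placebo arm's own result decide the matter, and neither says what an improvement is worth.

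Economic evaluation is in the trial's title and among its stated contributions. At stake is an economic conclusion that names the wrong arm, or a CEA that gives two opposite answers from the same data with nothing to settle between them. In the CUA no incremental result is named that could correct a wrong choice.

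**Working it through.** The section states no figure to reproduce, so the rule is checked by algebra and then by example.

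**Notation.** Placebo arm: cost C0, effect E0. UGSJB arm: cost C0 + c, effect E0 + e. Take the case that needs a decision rule: c > 0, e > 0, E0 > 0.

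**Equivalence.** UGSJB has the smaller average ratio when

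(C0 + c)/(E0 + e) < C0/E0.

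Cross-multiplying gives C0·E0 + c·E0 < C0·E0 + C0·e, that is c·E0 < C0·e, that is

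c/e < C0/E0.

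The left side is the ICER. So the smallest-average-ratio rule is an ICER rule with its threshold fixed at C0/E0. The same algebra holds for the ACUR.

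**Where the two stated rules disagree.** Let L be the threshold used for the ICER criterion.

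- If C0/E0 < ICER < L, the average rule selects placebo and the ICER rule calls UGSJB cost-effective.
- If L < ICER < C0/E0, the average rule selects UGSJB and the ICER rule does not call it cost-effective.
- If the ICER is below both or above both, the rules agree.

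**Inputs for illustration.** The effects are the CARS changes under Sample size calculation, taken as points of improvement: E0 = 4.6, E0 + e = 7.9, so e = 3.3. They come from a cited trial of herbal medicine plus behavioural education against behavioural education alone. Using them here is an assumption, as is using change as the denominator. The documents give no costs or threshold; the costs below are assumed, in arbitrary units.

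| Assumed costs (placebo, UGSJB) | ACER placebo | ACER UGSJB | Average rule selects | ICER | Conflict with ICER rule |
|---|---|---|---|---|---|
| 100, 180 | 100/4.6 = 21.7 | 180/7.9 = 22.8 | placebo | 80/3.3 = 24.2 | for any L above 24.2 |
| 1000, 1500 | 1000/4.6 = 217.4 | 1500/7.9 = 189.9 | UGSJB | 500/3.3 = 151.5 | for any L below 151.5 |

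With these effects the average rule switches at c/C0 = 3.3/4.6 = 0.717, whatever L is. The first row adds 80% to cost and is rejected; the second adds 50% and is accepted.

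**CUA.** With assumed utility gains of 0.02 and 0.03 and assumed costs of 500 and 800, the ACURs are 500/0.02 = 25,000 and 800/0.03 = 26,667, so placebo is selected. The incremental ratio is 300/0.01 = 30,000. The section does not name that ratio, so a threshold above 30,000 could not reverse the choice.

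**The case against.** The strongest reply has four parts.

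1. **Incremental analysis is partly planned.** The CEA already has an ICER with its own criterion, and a CBA is planned too. This stands and narrows the point. But the ICER is offered as an alternative to the ACER, the selection sentence is unconditional, and no rule is stated for the CBA. The CUA still names no incremental ratio.

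2. **The conflict depends on assumed costs and an unstated threshold.** True: it is possible, not certain. If UGSJB is both cheaper and more effective, the rules agree. The numerical threshold could properly be left to the analysis plan, and its absence is not part of this point.

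3. **The direction of error is not known.** A reader might infer that the rule is biased against UGSJB. The documents do not support that. With heavy shared costs, C0/E0 may be high and the likelier error is adopting UGSJB too readily, as in the second example.

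4. **The outcome scales might seem to make matters worse.** Under Secondary outcome measures, the EQ-5D-Y entry says "Lower scores indicate better quality of life", and a reader might infer that the CUA would reward the arm in worse health. The documents do not say that cost is divided by the raw score, and conversion to a utility is detail an article may leave to the full protocol or analysis plan. That reading is not supported.

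The economic evaluation is also not the primary objective; CARS is the primary outcome and the basis of the sample size. That limits the severity, not the correctness, of the point.

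**Conclusion.** The point holds, with moderate severity. The article states a selection rule on average ratios that is unsuited to an add-on comparison, sets an ICER criterion beside it without precedence, and gives the CUA only an average ratio. The equivalence with an ICER threshold of C0/E0 is exact when UGSJB costs more, works better and the placebo arm's effect is positive. It needs no outside figure.

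The numerical examples show that error is possible in both directions. They do not predict which will occur, because costs, threshold and the definition of the denominator are assumed. It would go too far to conclude that the trial will reach a wrong economic answer, or that no incremental analysis is planned. The CARS comparison, the other efficacy outcomes and the safety analysis are unaffected.

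**What to change.** Before the economic analysis is run, amend Economic evaluation as follows:

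- Delete the rule that selects the intervention with the smallest ACER or ACUR.
- Make the between-arm ICER the decision criterion for the CEA and an incremental cost-utility ratio the criterion for the CUA, or use net monetary benefit for both, judged against a threshold set in advance.
- Keep ACER and ACUR as descriptive results only.

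This changes analysis wording. It uses the cost and outcome data already planned and needs no new data collection or change in sample size.

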**Discussion:**

We prepared a well-designed clinical trial to investigate the safety and effectiveness of UGSJB on ASD symptoms compared with placebo treatment. The results from this study will provide clinical evidence on the safety, effectiveness, and economic value of UGSJB combined with acupuncture in children with ASD.

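### The ICER rule ignores the signs of the cost and effect differences, so as written it passes a costlier, less effective arm

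*Protocol article*

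**What the plan says.** The Economic evaluation section plans cost-effectiveness, cost-utility and cost-benefit analyses. The cost-effectiveness result is to be an average or an incremental ratio. The rule for the incremental ratio is one sentence: "Intervention with ICER below a certain level will be considered cost-effective". The article sets no requirement that the effect difference be positive, has no step for dominant or dominated arms, and gives no net-benefit form. Nothing elsewhere in it qualifies the sentence.

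On the denominator, "Effectiveness variables will be measured by ABC^2^, CARS, and CHQ-PF28". The article does not say whether CARS and ABC² enter as raw scores, where higher is worse, or are reversed so that higher is better. On the numerator, "Cost variables include medical and non-medical costs of patients and cost burden and productivity losses of guardians". No amounts are given. Both arms receive acupuncture ("Acupuncture, a treatment supported by the National Health Service in South Korea, will be provided to every participant for an economic evaluation"), so the planned difference between the arms is the granule.

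The Abstract makes the economic result one of the trial's main products: "The results from this study will provide clinical evidence on the safety, effectiveness, and economic value of UGSJB combined with acupuncture in children with ASD".

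**The concern.** A ratio does not keep the signs of its parts. Minus two can mean that UGSJB saves money and helps, or that it costs money and harms. A rule that looks only at whether the ratio lies below a level treats these two results alike.

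The problem lies in the criterion as stated, not in a missing detail. It holds for every non-negative level, so it does not matter that the article gives no value. It is also separate from the article's rule on average ratios. At stake is whether the stated criterion can support an economic conclusion when the observed effect is null or adverse.

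**Working it through.** **Signs.** Let ΔC be the cost difference and ΔE the effect difference, UGSJB minus placebo, with ΔE positive for benefit. Let L ≥ 0 be the level. The plan's rule is ΔC/ΔE < L. The net-benefit rule is L × ΔE − ΔC > 0.

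- If ΔE > 0, multiplying through by ΔE gives ΔC < L × ΔE. The two rules agree.
- If ΔE < 0, the inequality turns round and gives ΔC > L × ΔE, so net benefit is negative. The plan's rule then fires exactly when net benefit says no.

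The rule is therefore reversed in both quadrants where UGSJB works worse:

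- Costlier and worse: ΔC = 1, ΔE = −1 gives a ratio of −1, which is below any L ≥ 0, so it passes.
- Cheaper and worse: ΔC = −1, ΔE = −2 gives 0.5, which passes for any L above 0.5. Net benefit is 1 − 2L, which is negative for those same L.

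If raw CARS or ABC² is used, the sign of the denominator flips. A costlier arm that helps then always has a negative ratio. A costlier arm that harms passes once the harm is large enough. The ratio still does not separate the quadrants.

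**Inputs for the size.** From Sample size calculation: "The changes in CARS were −7.9 ± 5.42 for combination therapy and −4.6 ± 5.53 for behavioral education alone". The planned difference is 7.9 − 4.6 = 3.3 points, and the pooled SD is √((5.42² + 5.53²)/2) = 5.475.

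**The plan's own figure.** The normal formula gives n = 2 × (1.960 + 0.842)² × 5.475²/3.3² = 43.2, so 44. The exact t calculation gives 79.8% power at 44 and 80.7% at 45, so 45 per group is reproduced. 45/0.75 = 60 enrolled per group.

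**Standard error of ΔE.** 5.475 × √(2/45) = 1.154 points at 45 per arm, and 5.475 × √(2/60) = 1.000 at 60.

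**Firing rates with no true effect.** Assume ΔC > 0 and fixed, and let d = ΔC/L be the break-even gain in CARS points.

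- Plan's rule: P(ΔE < 0) + P(ΔE > d) = 0.5 + [1 − Φ(d/SE)]
- Net benefit: P(ΔE > d) = 1 − Φ(d/SE)

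For d = 1 and 45 per arm: d/SE = 1/1.154 = 0.866 and 1 − Φ(0.866) = 0.193. The plan's rule fires 69.3% and net benefit 19.3%.

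| Break-even gain d (points) | Plan's rule, 45 per arm | Net benefit, 45 per arm | Plan's rule, 60 per arm |
|---|---|---|---|
| 0.5 | 83.2% | 33.2% | 80.8% |
| 1 | 69.3% | 19.3% | 65.9% |
| 2 | 54.2% | 4.2% | 52.3% |
| 3.3 | 50.2% | 0.2% | 50.0% |

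In every row, 50 percentage points of the plan's rate come from results in which UGSJB is costlier and less effective. That floor does not depend on the sample size. By symmetry the rates are the same with raw scores.

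**Relaxing the fixed cost.** If ΔC varies independently of a symmetric ΔE, the rate is 0.5 × [1 + P(|ΔC| < L × |ΔE|)], still at least one half. Independence matters. The following simulated rates use 60 per arm, cost in arbitrary units with standard error 1, and correlation 0.9 between ΔC and ΔE:

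- Mean ΔC of 1: 34% at L = 0, 46% at L = 0.5, 51% at L = 1.
- Mean ΔC of 0: 14% at L = 0.

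**The case against.** The strongest reply is that the section is a short summary. The level is visibly a placeholder, and any health economist would check for dominance before quoting a ratio. A full protocol or analysis plan may say so. Part of this stands: the value of the level, the bootstrap details and the acceptability curve may properly be left to a fuller document and are not criticised here. What remains is that the article does state a criterion, and that criterion gives the wrong answer whenever the effect difference is negative. Condensing a rule does not require stating it in a form that fails.

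A second reply is that the rates rest on an assumed cost difference. That also stands. The costs include guardians' burden and productivity losses, which could move with the child's outcome, so a correlation between cost and effect is possible. The rates are conditional and are given as such.

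A third is that the rule uses a point estimate. So does net benefit above zero, so this does not count against the present sentence in particular.

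A reader might go further and infer that the rule favours a harmful product over a useful one. The plan's figures do not bear that out. At 45 per arm, a true 3.3-point benefit against a true 1-point harm fires 99.4% against 90.4% at d = 0.5, 97.9% against 84.8% at d = 1, and 87.2% against 81.2% at d = 2. The order reverses only at d = 3.3 (50.2% against 80.7%). There the true gain equals the break-even gain, and net benefit also fires 50%.

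A reader might also infer that a null trial would most likely be reported as cost-effective. That assumes analysts would apply the sentence mechanically and ignore the CARS comparison and the cost-benefit analysis, both of which are planned. The document does not support that prediction.

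**Conclusion.** The concern holds for the rule as written. With benefit-coded effects and a non-negative level, the ICER sentence passes a costlier, less effective arm and reverses the judgement on a cheaper, less effective one. Raw scores change which quadrant fails but do not cure it.

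The size depends on two assumptions: UGSJB costs more, and its cost difference is fixed or independent of the effect difference. Under these, with no effect on CARS, the rule fires between 50% and 83% of the time at 45 per arm for break-even gains from 3.3 down to 0.5 points, against 0.2% to 33% for net benefit. A floor of one half that holds in all circumstances is not supported: with strong positive correlation and an uncertain cost difference, rates of 14% to 46% arise. The algebra of the signs needs no cost figure at all.

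**What to change.** Replace the ICER sentence with wording such as:

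> *UGSJB will be considered cost-effective if its incremental net benefit versus placebo, L × ΔE − ΔC, with ΔE coded so that positive is benefit, is above zero; it will be reported with a 95% CI. Dominance will be classified first, and an ICER will be quoted only when UGSJB is both costlier and more effective.*

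The coding clause means that CARS and ABC² changes are reversed in sign before use, while CHQ-PF28 is kept as scored. Under this rule a dominated arm cannot pass.

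The cost is one sentence and a little more analysis of cost and outcome data already planned. No treatment, visit or sample size changes. The downside for the investigators is that a favourable economic conclusion becomes less likely.
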